**PHOTOGRAPHS OF RASH OR INJECTION SITE REACTIONS**

If a volunteer develops a rash or injection site reaction, photographs may be taken by the investigators. These photographs will not include the participant's face or any identifying scars, marks, or tattoos.

**CONTRAINDICATIONS TO VACCINATION**

The following criteria should be checked prior to each immunization and are contraindications to further immunization. The participant will be encouraged to remain in the safety evaluation for doses already received.

- Hypersensitivity reaction following administration of the study vaccine.
- Positive urine or serum  $\beta$ -hCG test.
- Urine dipstick more than trace positive for blood or protein, confirmed by urinalysis. Should a female participant's urine dipstick show more than trace blood, she will not be excluded from vaccination if she is currently menstruating.

**INDICATIONS FOR DEFERRAL OF VACCINATION**

If any one of the following adverse events occurs at the time of the scheduled vaccination, the participant may be either vaccinated at a later date within the allowable time interval specified in the protocol or withdrawn at the discretion of the Investigator:

- Oral temperature  $>37.5^{\circ}\text{C}$  at the time of vaccination will warrant deferral of immunization until fever resolves (within protocol-defined vaccination window).
- Any other condition that in the opinion of the Investigator poses a threat to the individual if immunized or that may complicate interpretation of the safety of vaccine following immunization.

Such individual(s) will be followed in the clinic until the symptoms resolve or the window for immunization expires. No further vaccination will be performed if the participant does not recover (oral temperature  $\leq 37.5^{\circ}\text{C}$  and/or lack of symptoms) within the vaccination window described in **Section 6.5** of this protocol. The participant will be monitored for safety and immunogenicity. If the subject does not receive the second vaccination, some scheduled safety blood draws may not be performed at the discretion of the Principal Investigator. Blood draws scheduled to measure immune response will be obtained if possible. If the individual meets any of the above criteria for deferral on the day of first immunization, the Investigator may elect to exclude the participant from further participation in the study. Eligible alternates will be vaccinated instead.

### **SUBJECT WITHDRAWAL CRITERIA**

A volunteer will not be considered to have completed the trial if any of the following reasons apply:

1. *Research terminated by Sponsor or Investigator* – applies to the situation where the entire study is terminated by the Sponsor or Investigator, or other regulatory authority for any reason.
2. *Withdrawal of consent* – applies to a subject who withdraws consent to participate in the study for any reason.
3. *Noncompliant with protocol* - applies to a volunteer who does not comply with protocol-specific visits or evaluations, on a consistent basis, such that adequate follow-up is not possible and the volunteer's safety would be compromised by continuing in the trial. This also applies to a volunteer who is lost to follow-up and is not reachable by telephone or other means of communication; and is not able to be located.
4. *Developed an Adverse Event* - applies to a participant who is withdrawn from study due to an adverse event, serious or otherwise.
5. *Other* – is used when previous categories do not apply and a written explanation is required.

If a subject withdraws or is withdrawn prior to completion of the study, the reason for this decision will be recorded in the case report forms. Any volunteer who has received at least 1 dose of vaccine will be encouraged to remain in the safety evaluation for the duration of the study. The subject's data will be included in the safety and immunogenicity analysis. If a subject is withdrawn because of an AE or SAE, the participant will be followed until resolution or stabilization of the event.

### **REPLACEMENT OF SUBJECTS**

Subjects who withdraw or are terminated from the study prior to completion will not be replaced.

### **TREATMENTS THAT COULD POTENTIALLY INTERFERE WITH VACCINE-INDUCED IMMUNITY**

Treatment with any of the following medications during the study may exclude a subject from receiving further doses of the study vaccine. However, the subject will be encouraged to remain in the study for the duration of the study for safety evaluations.

- Licensed vaccine in the 2-week period prior to and following each vaccination
- Receipt of immunoglobulins and/or any blood products up to 30 days after administration of the last dose of vaccine
- Chronic oral or intravenous administration ( $\geq 14$  days) of immunosuppressive doses of steroids, i.e., prednisone  $>10$  mg per day, immunosuppressants or other immune-modifying drugs from each day of vaccination to two weeks following each vaccination
- Any investigational drug or investigational vaccine other than the study vaccine during the study period
- Chloroquine or related compounds (amodiaquine or primaquine) during the study period

### **CLINICAL LABORATORY TESTING**

Using standard techniques, the clinical laboratory will perform the following tests:

1. Complete blood count plus white blood cell differential and platelet count\*
2. Serum creatinine
3. Alanine aminotransferase (ALT)
4. HIV assay (FDA-approved screening antibody assay with Western Blot Confirmation) (US only)
5. HBsAg ELISA (US) or rapid diagnostic test (Mali)
6. HCV assay (FDA-approved screening antibody assay and immunoblot confirmation or viral PCR confirmation (US) or rapid diagnostic test (Mali)
7. Urinalysis (in the event of an abnormal urine dipstick test at the clinical trial site)\*\*
8. Anti-dsDNA (ELISA)
9. Urine for chloroquine determination (Mali)
10. Malaria smear (Mali)

\* The following CBC parameters will be assessed for safety throughout the trial: WBC, ANC (absolute neutrophil count) and/or absolute granulocyte count, Hemoglobin, and Platelet Count.

\*\* Urine and serum  $\beta$ -hCG testing will be performed at the clinical trial site using an FDA approved product.

### **IMMUNOLOGIC LABORATORY TESTING**

#### **6.1.1 Antibody Assay (ELISA)**

Anti-AMA1 and anti-MSP142 ELISAs will be performed at the Malaria Research and Training Center in Mali and/or the Laboratory of Malaria Immunology and Vaccinology (LMIV) in Rockville, MD. Antibody levels to the 2 antigens will be measured in serum by ELISA. Duplicate assays will be done for both 3D7 and FVO forms of the proteins. Briefly, microwell plates are coated with antigen solution. Plates are washed with TRIS-buffered saline (TBS)

containing Tween-20 (T-TBS) and blocked with TBS containing skim milk powder. After washing with T-TBS, diluted serum samples are added in triplicate and incubated at room temperature for 2 hours. After incubation, unbound antibodies are removed by washing the plates with T-TBS, and alkaline phosphatase-conjugated goat anti-human IgG solution is added to each well and incubated for 2 hours at room temperature. Plates are then washed with T-TBS, followed by adding phosphatase substrate solution to each well; the plates are then covered and incubated for 20 minutes at room temperature for color development. The plates are read immediately at 405 nm with a microplate reader. The optical density values are used to determine antibody levels by comparing to a standard curve generated from a known positive-control plasma included on each ELISA plate.

#### 6.1.2 Growth Inhibition Assay (GIA)

GIAs will be done at the Laboratory for Malaria and Vector Research (LMVR) in Rockville, MD. The GIA is designed to determine whether antibodies obtained from an immunized person can inhibit the process of merozoite invasion into red cells. In this assay, synchronized blood-stage parasites from the FVO and 3D7 lines are incubated *in vitro* with purified IgG from subject sera for a period of 40 hours. During this period, merozoites emerge from the infected red blood cells, invade normal red blood cells, and initiate a new growth cycle. Growth is determined by measuring the production of parasite lactate dehydrogenase activity. The percentage reduction in the number of newly invaded red blood cells in the presence of the post vaccination IgG compared to the number of newly invaded red blood cells in the presence of the Day 0 purified IgG is calculated as the growth inhibitory activity.

#### 6.1.3 B-Cell Assays

B-cell studies will be done at the Malaria Research and Training Center (MRTC) in Mali or the LMIV in Rockville, MD. The analysis of the generation and maintenance of antigen-specific memory B cells will be carried out to determine if these cells can be elicited and maintained by vaccination both in malaria-naïve and semi-immune adults. Peripheral blood lymphocytes will be obtained and assayed for the presence of antigen-specific memory B cells and for the total number of memory B cells using flow cytometry and ELISPOT assays.

#### 6.1.4 T-Cell Assays

T-cell studies will be done at LMVR, in Rockville, MD, or at MRTC and LMIV. Antigen-specific T-cell responses to vaccination will be determined by ELISPOT and by measurement of cytokine levels in supernatants of peripheral blood mononuclear cells. Specimens collected for B cells and T cells will undergo initial processing and cell separation at the CIR-DC and MRTC, and will be shipped to LMIV and distributed to LIG and LMVR in liquid nitrogen shippers as per SOP.

#### 6.1.5 Filter paper

Filter paper will be collected in Mali at specified time points and at unscheduled visits when malaria smears are performed. Filter papers will be stored at MRTC and will be analyzed to determine the genotype of infecting malaria species if clinical data suggest a difference between the vaccine and comparator groups.

## **7. USE, STORAGE, AND TRACKING OF SPECIMENS AND DATA**

Samples and data collected under this protocol will be used to study malaria and related diseases, and possible adverse reactions to vaccination. No genetic testing will be performed. Access to research samples will be limited using either a locked room or a locked freezer. Samples and data will be stored using codes assigned by the investigators or their designees. Data will be kept in password-protected computers. Only investigators or their designees will have access to the samples and data.

Samples will be stored at the LMIV in Rockville, MD or at LMIV's designated repository, Thermo Scientific, Rockville, MD, or at the MRTC in Bamako, Mali. Samples will be tracked using a sample tracking software program, e.g., Freezerworks. Any loss or unanticipated destruction of samples (for example, due to freezer malfunction) or data (for example, misplacing a printout of data with identifiers) will be reported to the IRBs. Such a loss will be reported to the NIAID IRB as a protocol violation under the following classification: the violation compromises the scientific integrity of the data collected for the study.

## **8. RETENTION OF SPECIMENS FOR FUTURE USE**

All specimens collected as part of this trial may, with the subject's permission, be stored for future research. Whether or not a volunteer agrees to storage of specimens will not affect his/her ability to participate in this trial. These samples may be used to learn more about malaria infection and other diseases. These samples will not be sold or used to make commercial products. Samples will be stored only with the volunteer's permission. The volunteer may withdraw permission for future use of specimens at any time. If a volunteer withdraws his or her permission for future use of specimens, those specimens will be destroyed. All samples stored will be labeled with the volunteer's study identification (ID) number, which cannot identify the study subject but is linkable to other research databases (e.g., from questionnaires, clinical assessments, logbooks, etc.) generated by the main study. The database will contain only the study volunteer's ID number. A master log linking the study volunteer ID number to the name of the volunteer will be maintained in a password protected database system with access limited to authorized research team members.

At the completion of the protocol (termination), samples and data will either be destroyed, or transferred to another existing protocol, "Research Use of Human Specimens", NIAID Protocol #08-I-N064 or a repository. In the future, other investigators (both at NIH and outside) may wish to study these samples and/or data. In that case, IRB approval must be sought prior to any sharing of samples. Any clinical information shared about the sample with or without patient identifiers would similarly require prior IRB approval. The research use of stored, unlinked, or unidentified samples (for example, as a standard for immunological analyses) may be exempt from the need for prospective IRB review and approval. Exemption requests will be submitted in writing to the NIH Office of Human Subjects Research, which is authorized to determine whether a research activity is exempt. The FMPOS ethics committee will approve additional research on stored samples collected under this protocol, even if such research has been determined to be exempt from NIAID IRB review.

## 9. ASSESSMENT OF SAFETY

### DOCUMENTING, RECORDING AND REPORTING OF ADVERSE EVENTS

At each contact with the subject, information regarding adverse events will be elicited by appropriate questioning and examinations and will be immediately documented on a source document, recorded on the Adverse Event Case Report Form (AE CRF) or electronic database and reported to the IND Sponsor, IRB and FDA as outlined below.

### DEFINITIONS

#### ADVERSE EVENTS (AE)

An adverse event (AE) includes any unfavorable or unintended change in anatomical, physiological, or metabolic functions as indicated by physical signs, symptoms, and/or laboratory-detected changes occurring in any phase of the clinical study, whether associated with the study vaccine or active comparator, and whether or not considered vaccination related. This includes an exacerbation of pre-existing conditions and intercurrent illnesses. All AEs must be graded for severity and assessed for relationship to the investigational vaccine as described below.

#### Adverse Reaction (AR)

An adverse event that is caused by an investigational agent (drug or biologic)

#### Suspected Adverse Reaction (SAR)

An adverse event for which there is a reasonable possibility that the investigational agent caused the adverse event. "Reasonable possibility" means that there is evidence to suggest a causal relationship between the drug and the adverse event. A suspected adverse reaction implies a lesser degree of certainty about causality than adverse reaction which implies a high degree of certainty.

### SERIOUS ADVERSE EVENTS

A serious adverse event (SAE) is an AE, whether considered related to the investigational vaccine or not, resulting in one of the following outcomes:

1. Death during the period of protocol-defined surveillance.
2. Life threatening event: defined as an event that places a subject at immediate risk of death at the time of the event and does not refer to an event that hypothetically might have caused death were it more severe.
3. Hospitalization or prolongation of a hospitalization during the period of protocol-defined surveillance: defined as at least an overnight stay in the hospital or emergency ward for treatment that would have been inappropriate if administered in the outpatient setting.
4. A congenital anomaly or birth defect.
5. A persistent or significant incapacity or substantial disruption of the ability to carry out normal life functions.
6. Any other important medical event that may not result in death, be life threatening, or require hospitalization, may be considered a serious AE when, based upon appropriate medical

judgment, the event may jeopardize the subject and may require medical or surgical intervention to prevent one of the outcomes listed above.

### **Unexpected Adverse Event**

An AE is unexpected if it is not listed in the Investigator's Brochure or Package Insert (for marketed products) or is not listed at the specificity or severity that has been observed. It is the responsibility of the IND Sponsor to make this determination.

### **Suspected and Unexpected Serious Adverse Reaction (SUSAR)**

A SUSAR is a Suspected Adverse Reaction that is both Serious and Unexpected.

### **Unanticipated Problem (UP)**

An Unanticipated Problem is any event, incident, experience, or outcome that is:

1. unexpected in terms of nature, severity or frequency in relation to the research risks that are described in the IRB-approved protocol, informed consent document, Investigator's Brochure, or other study documents and the characteristics of the subject population being studied; and
2. possibly, probably, or definitely related to participation in the research; and
3. places subjects or others at a greater risk of harm (including physical, psychological, economic or social harm) than was previously known or recognized. (Per the IND Sponsor, an AE with a serious outcome will be considered increased risk.)

### **Unanticipated Problem That is Not An Adverse Event (UPnonAE)**

A UP that does not fit the definition of an AE, but which may, in the opinion of the Investigator, involve risk to the subject, affect others in the research study or significantly impact the integrity of research data. Examples include occurrences of breaches of confidentiality, accidental destruction of study records, and unaccounted study drug.

### **Protocol Violation**

A Protocol Violation is any change, divergence, or departure from the study design or procedures in an IRB-approved research protocol that has a major impact on the subject's rights, safety, or well-being and/or the completeness, accuracy or reliability of the study data.

### **Protocol Deviation**

A Protocol Deviation is any change, divergence, or departure from the study design or procedures of an IRB-approved research protocol that does not have a major impact on the subject's rights, safety or well-being, and/or the completeness, accuracy and reliability of the study data.

## **ASSESSMENT OF ADVERSE EVENTS**

### **9.1.1 Identification of Adverse Events**

Assessment of safety will include clinical observation and monitoring of hematological, chemical, and immunologic parameters. Safety will be evaluated by monitoring of subjects for local and systemic adverse reactions during the course of the trial. Subjects will be closely monitored for 30 minutes following each immunization. Additionally, subjects will return to the

clinic on Days 1, (Mali only) 2, (Mali only) 3, 7, and 14 following each vaccination for clinical assessments, and approximately monthly thereafter until completion.

All AEs will be graded for severity and assessed for relationship to the study product. Reactions will be graded as described in **Section 9.1.2** in this protocol. A study clinician will be available 24 hours a day during the study evaluation period; a study clinician will stay in Bancoumana for the duration of the trial and will be available to the study participants at all times. Should a subject call on a study clinician to report an adverse event, it will be fully documented in the subject's study chart, and discussed with the Principal Investigator.

All local and systemic reactions will be captured on the appropriate case report form (CRF). Those assessed as serious will be further reported on the Sponsor's SAE report form. Adverse events judged to be possibly, probably, or definitely related to the study product will be followed to adequate resolution.

#### 9.1.2 Determination of Severity

Severity of AEs will be assessed by the investigator as described in **Appendixes C, D, and E**. AEs not included in the Appendixes will be graded for severity using the followings definitions:

|                             |                                                                                                                                                                  |
|-----------------------------|------------------------------------------------------------------------------------------------------------------------------------------------------------------|
| Grade 1 (Mild):             | No effect on activities of daily living                                                                                                                          |
| Grade 2 (Moderate):         | Partial limitation in activities of daily living (can complete $\geq 50\%$ of baseline), or treatment given; no or minimal medical intervention/therapy required |
| Grade 3 (Severe):           | Activities of daily living limited to $< 50\%$ of baseline, medical evaluation/therapy required                                                                  |
| Grade 4 (Life-threatening): | Extreme limitation in activity, significant assistance required; immediate medical intervention or therapy required to prevent death                             |
| Grade 5:                    | Death                                                                                                                                                            |

#### 9.1.3 Association with Receipt of the Study Vaccine

All AEs will be assessed for relationship to the study vaccine using the following definition:

|                     |                                                                                                                                                                                                                                                                    |
|---------------------|--------------------------------------------------------------------------------------------------------------------------------------------------------------------------------------------------------------------------------------------------------------------|
| Definitely:  | Clear-cut temporal association, and no other possible cause.                                                                                                                                                                                                       |
| Probably:    | Clear-cut temporal association and a potential alternative cause is not apparent.                                                                                                                                                                                  |
| Possibly:    | Less clear temporal association; other causes also possible.                                                                                                                                                                                                       |
| Unlikely:    | Temporal association between the AE and the vaccine or the nature of the event is such that the vaccine is not likely to have had any reasonable association with the observed illness/event (cause and effect relationship improbable but not impossible). |
| Not Related: | The AE is completely independent of vaccine administration; and/or evidence exists that the event is definitely related to another cause.                                                                                                                          |

The degree of certainty with which an AE can be attributed to administration of the study vaccine will be determined by how well the event can be understood in terms of one or more of the following:

1. The event being temporally related with vaccination or reproduced on re-vaccination
2. A reaction of similar nature having previously been observed with this type of vaccine and/or formulation
3. The event having been reported in the literature for similar types of vaccines

All local (injection-site) reactions will be considered causally related to vaccination. [Episodes of clinical malaria will be considered as not related to vaccination.]

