## **INVESTIGATOR REPORTING RESPONSIBILITIES TO THE NIAID IRB**

### **Expedited Reporting to the NIAID IRB**

Unanticipated problems that are either AEs or non-AEs and protocol violations will be reported within 7 calendar days of site awareness. Serious Adverse Events that are possibly, probably, or definitely related to the research will be reported to the NIAID IRB within 7 days of site awareness, regardless of expectedness. Investigators will report within 15 days on any other event or condition regardless of grade, which in their judgment represents an event reportable to the NIAID IRB.

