## **HALTING RULES**

The Principal Investigator will closely monitor study data as they become available and will make determinations regarding the presence and grading of adverse events. Adverse events will be evaluated with regard to the known complications associated with administration of CPG 7909 and other vaccine components. If a dose of vaccine is considered unacceptably reactogenic (as described in the following criteria), the study will be halted. No new enrollments and no further vaccinations will be administered by the Investigators until reviewed by the SMC and study IND Sponsor. A report of SMC recommendations will be submitted to the IRB. The following criteria will be used to define unacceptable reactogenicity of the malaria vaccine:

1. One or more subjects experience an SAE as defined in **Section 9.2** of this protocol that is determined to be possibly, probably, or definitely related to the vaccine, **or**
2. One or more subjects experience a hypersensitivity reaction that is probably or definitely related to the vaccine, **or**
3. Any severe clinical illness occurs that is not explained by a diagnosis that is unrelated to vaccination, **or**
4. Two or more subjects in any dose cohort (low dose US, high dose US, or Mali) experience any Grade 2 or higher laboratory abnormality (see **Appendix D**), or Grade 3 systemic AE that is determined to be possibly, probably, or definitely related to the vaccine as defined in this protocol. This does not include Grade 2 neutropenia resolving within 7 days of vaccination, which is an expected laboratory abnormality with CPG 7909 and which has not been associated with clinically significant events.

The IRBs, the NIAID, the pharmaceutical supporter(s), the FDA, or other government agencies, may discontinue the study at any time. Subsequent review of serious, unexpected, and related adverse events by the Medical Monitor, SMC or IRB, the IND sponsor, the FDA, and other regulatory authorities may also result in suspension of further administration of vaccine at the clinical site. The FDA, other regulatory authorities, and the study sponsor(s) retain the authority to suspend additional enrollment and administration of vaccine for the entire study as applicable.

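### Section 9.1.3 fixes all clinical malaria as unrelated to vaccination with no exception for serious episodes, so a serious episode cannot set off the automatic safety rules

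*Protocol*

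**What the plan says.** Two places require every adverse event to be judged for relationship. The definition of adverse events in Section 9, which includes intercurrent illness, says "All AEs must be graded for severity and assessed for relationship to the investigational vaccine as described below". Section 9.1.3 says "All AEs will be assessed for relationship to the study vaccine using the following definition" and gives a five-level scale. Its lowest level, Not Related, includes the case where "evidence exists that the event is definitely related to another cause".

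The same section closes with two rules set in advance. All injection-site reactions count as caused by vaccination. Then, in square brackets: "Episodes of clinical malaria will be considered as not related to vaccination". No limit by severity, seriousness, timing or outcome is attached.

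Several later rules depend on the relationship judgement:

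- Halting rule 1: "One or more subjects experience an SAE as defined in" the serious-event section, provided it is judged at least possibly related to the vaccine.
- Halting rule 3: a severe clinical illness, unless a diagnosis unrelated to vaccination explains it.
- Halting rule 4, systemic branch: two or more subjects in a cohort with a "Grade 3 systemic AE that is determined to be possibly, probably, or definitely related to the vaccine as defined in this protocol".
- Expedited Reporting to the NIAID IRB: "Serious Adverse Events that are possibly, probably, or definitely related to the research will be reported to the NIAID IRB within 7 days".
- Sponsor's Reporting Responsibilities: expedited FDA reports cover serious, unexpected suspected reactions, and deaths or life-threatening events with any possible relationship to the intervention.

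**The concern.** A recombinant protein vaccine cannot give anyone malaria, so labelling an ordinary episode as unrelated is sensible. Whether vaccination made an episode worse is a different question, and the protocol does not treat it as closed. The discussion of immunization risks in Section 12 says that CPG 7909 may have a different safety profile in malaria-endemic populations. The account of earlier AMA1-C1/Alhydrogel trials reports a paediatric study in which mean haemoglobin during clinical malaria was lower with vaccine (9.95 against 10.33 g/dL). That difference was not significant after correction for multiple tests, and extended follow-up showed no significant difference. This is not evidence of harm, but it is a reason not to settle causality in advance for the worst cases.

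The Overall Design section expects that Malian participants may have malaria infection during the vaccination period, so doses can still be outstanding when an episode occurs. If a vaccinee then had a serious episode, the pause for review that rule 1 is meant to impose would not follow.

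**Working it through.** The plan states no figure on this point. The check is a reading of the text, followed by an illustration of size.

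**Step 1. Following a serious malaria episode through the rules as written.**

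| Rule | Needs | Result for serious malaria |
|---|---|---|
| Adverse event definition; 9.1.3 scale | Assessment of relationship | Replaced by a fixed label of not related |
| Halting rule 1 | One serious event, at least possibly related | Cannot be met |
| Halting rule 3 | Severe illness not explained by an unrelated diagnosis | Treated as explained, so not met |
| NIAID IRB, 7 days | Serious event at least possibly related to the research | Missed on the natural reading; goes to continuing review |
| FDA, expedited | Suspected reaction, or any possible relationship | Missed on the natural reading |

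**Step 2. What still operates.** Under the investigator's reporting duties to the sponsor, serious events go to the sponsor within 1 or 3 business days whatever their cause, and to LMIV within 1 working day. Those in Mali also go to the Medical Monitor within 1 working day. The Medical Monitor may ask for a Safety Monitoring Committee meeting, and the committee may also meet at its own or the investigators' discretion. The investigator has a discretionary 15-day report to the NIAID IRB. Local ethics committee rules apply, and the Institutional Review Board section of Section 12 has the investigator notify the IRB of serious events without a relatedness condition, though also without a deadline. None of these routes halts dosing automatically.

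**Step 3. How often it could matter for rule 1.** Inputs:

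- 15 vaccinees and 30 participants in all in Mali (Overall Design).
- Dose 3 on Day 120 in Mali (Section 6, Clinical Monitoring and Evaluation). Afterwards there is no dose left to stop.
- 12-month risk p of serious malaria: not given anywhere. Assumed 0.5%, 1% or 2%, spread evenly over 360 days.

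Risk before dose 3 is p × 120/360 = p/3. The chance of at least one case among n people is 1 − (1 − p/3)^n.

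| Assumed p | p/3 | n = 15 vaccinees | n = 30, both arms |
|---|---|---|---|
| 0.5% | 0.00167 | 1 − 0.9753 = 2.5% | 1 − 0.9512 = 4.9% |
| 1% | 0.00333 | 1 − 0.9511 = 4.9% | 1 − 0.9047 = 9.5% |
| 2% | 0.00667 | 1 − 0.9045 = 9.5% | 1 − 0.8182 = 18.2% |

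The n = 15 column bounds the chance that a vaccinee's episode would have counted. The n = 30 column bounds the chance of a rule 1 halt for malaria after the fix, since the assessor is blinded and a comparator recipient's episode could also be judged possibly related. Both are upper bounds: the episode must still be judged at least possibly related, and dose 3 is timed just before the transmission season, so risk before Day 120 should be below an even share. Under the present sentence the chance that such an episode counts is zero.

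**The case against.** The best defence is that the sentence only applies the Not Related definition in advance. Diagnosed malaria has a definite parasitic cause, and injection-site reactions are handled by a similar blanket rule. That stands for ordinary malaria, so a reader who infers that the sentence contradicts the assessment requirement for all malaria goes too far. It does not stand for serious episodes, where the open question is contribution to severity rather than cause of infection.

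A second defence is that relation to vaccination is narrower than relation to the research, the test used for the NIAID IRB, and that other IRB routes remain. This stands in part. The 7-day report is missed on the natural reading, not by strict necessity, and it would be wrong to infer that the IRBs or the sponsor would not hear of the event.

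A third is that comparisons between arms are the better tool for detecting vaccine-modified malaria. The primary analysis compares the proportion with any adverse event by arm whatever the relationship, and filter papers can be genotyped if the groups differ. True, but these analyses do not pause dosing.

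Three stronger readings are tempting and not supported:

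- *That vaccine reactions labelled as malaria would seriously weaken rule 4.* The Grade 3 malaise, fever and headache seen in US volunteers do resemble malaria, but the protocol gives no basis for any misdiagnosis fraction. Fever, headache and malaise are solicited events with their own grades, and smears are taken on dosing days. Misdiagnosis is a matter of case definition, separate from this sentence.
- *That the exception should reach every Grade 3 episode.* For events not listed in the appendixes, Section 9.1.2 sets Grade 3 at "Activities of daily living limited to" less than half of baseline, with medical evaluation or therapy needed. An ordinary bed-bound episode could qualify. If the risk of Grade 3 malaria before dose 3 were 2%, 5% or 10% (assumed) in the 30 Mali participants, the chance of two or more, 1 − (1 − p)^30 − 30p(1 − p)^29, would be 12%, 45% or 82%. That is an upper bound on rule 4 halts, but too high a price for the purpose.
- *That the earlier paediatric deaths show vaccine-worsened malaria.* The protocol does not say that those events were malaria.

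**Conclusion.** The point holds for serious malaria and is minor. A fixed label removes a required judgement and with it the one automatic halt that a single serious event should be able to trigger; the expedited IRB and FDA reports go with it on the natural reading. What is lost is the automatic triggers, not oversight.

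The size is small. On the assumed risks, the chance that a vaccinee has a serious episode while a dose remains is at most about 2.5% to 9.5%. A reader might use the full 12-month risk and obtain 7%, 14% or 26% (1 − (1 − p)^15 for the same p). Those figures overstate the effect on halting, because episodes after dose 3 leave nothing to stop. Serious disease should also be uncommon: the introduction says that people who survive early childhood in endemic areas rarely succumb to life-threatening malaria.

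The conclusion about the text needs none of these assumptions. The percentages depend on all of them, since the protocol gives no malaria rate. The square brackets suggest that the sentence may be unsettled template text, but it stands in the current protocol and has to be confirmed, limited or removed.

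**What to change.** Replace the bracketed sentence in Section 9.1.3 with:

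*Episodes of clinical malaria that are not serious will be considered not related to vaccination; any episode meeting the SAE definition will be assessed for relationship case by case by the blinded assessor using the definitions above.*

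This keeps the convention where it is sound, reopens rule 1 and the expedited reports for serious episodes, and leaves Grade 3 episodes that are not serious outside rule 4.

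The cost is one sentence and no new data. The downside is a slightly higher chance of a precautionary halt under rule 1, at most about 5%, 9.5% or 18% across both arms for the assumed 12-month risks of 0.5%, 1% or 2%. Such a halt is a pause until the Safety Monitoring Committee and the sponsor have reviewed the case, not an end to the trial.
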